### Data Collection

Measurements for most scales will be conducted at the beginning of the trial (T0), after every 10 sessions (T10, T20, and T30), and 1 month after trial completion (T60; Table 1). Trained psychiatrists, psychiatric residents, and/or medical students will complete all assessments. Data will be collected directly using the REDCap electronic data capture tools.

Recorded entrance and exit interviews will be stored in an encrypted database and have identifying information stripped from them on a rolling basis. This database may then be analyzed in future studies.

Participants will perform the auditory lexical decision task on tablet devices using a previously developed app. They will first answer questions on their age, handedness, native languages, other spoken languages, age at which they began to learn English, English-speaking countries they have visited, and whether or not they grew up in western Canada. They will then hear a series of 200 stimuli and must mark whether they think each stimulus is a real or fictious word. There are a total of 2000 words split into 32 different lists. Participants will perform this task before commencing treatment (T0), after each stimulation session (T1-30), and 1 month after trial completion (T60).

There are 3 validated versions of the SCIP. To prevent participants from improving their scores by way of repeated exposure, version 1 will be administered at baseline, version 2 after the 30 treatments are delivered, and version 3 at the 1-month postcompletion assessment.

**Table 1 table1:** Schedule of assessments.

Assessment			Timepoint								
			Enrollment and baseline^a^		Treatment period^b^						Follow-up^c^
			T0		T1-9; T11-19; T21-29		T10; T20		T30		T60

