### Safety

In a meta-analysis examining over 33,200 sessions of tDCS, no serious adverse events were identified [23]. Common side effects of treatment that occur in up to 50% of patients include mild-to-moderate skin erythema, itchiness, tingling at electrode sites, or mild headache [20,24]. Less commonly observed side effects that have been reported include tinnitus, nervousness, light-headedness, blurred or brighter vision, reduced concentration, nausea, mild euphoria, fatigue, insomnia, or constriction when swallowing. When they occur, these side effects are generally transient and of low intensity.

In patients with bipolar depression, tDCS may rarely induce a manic or hypomanic switch. In a randomized control trial evaluating the use of tDCS in bipolar depression, treatment-emergent affective switches were observed in 15% of patients; however, these did not meet the criteria for hypomanic or manic episodes and did not require hospitalization or treatment discontinuation [25].

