### Intervention and Control

In addition to continuing their usual pharmacological and psychological treatments, participants in both arms will receive 30 sessions of either sham or active tDCS, 5 days per week, for a total of 6 weeks, using a Sooma stimulator (Sooma Oy). This constitutes twice the number of treatment sessions as that used in the longest previously conducted study of tDCS in treatment-resistant depression [20]. For both groups, the anode will be positioned over the left DLPFC (position F3 on the 10-20 EEG system), and the cathode will be positioned over the right DLPFC (position F4). Electrodes will be positioned using the caps supplied by Sooma, with participant head circumference measured first to ensure that the proper-sized cap is applied. Each electrode pad will be saturated with 15 mL of normal saline before application.

Participants will be blinded to the group to which they have been assigned. Two stimulators labeled only as *A* and *B* will be set to provide either sham or active stimulation by an investigator not involved in participant interaction or data collection. In the sham group, the applied current will ramp up from 0.3 mA to 2 mA over 17 seconds and then ramp down to 0.3 mA over 17 seconds, where it will be maintained for the duration of the 30-minute session. Previous trials have demonstrated that this short period of active stimulation is an effective way of triggering scalp tingling at a total dose of tDCS believed to be below the threshold for inducing neuroplasticity changes [32,33]. Current must be maintained at 0.3 mA to allow for operation of the electrode-contact sensors; if these were deactivated entirely, blinding would be broken. In the active intervention group, the applied current will ramp up to 2 mA over 17 seconds and be maintained at that level for 30 minutes, before gradually ramping down.

Participants will be withdrawn from the study if they miss two consecutive treatments or more than five treatments in total, if they undergo a serious adverse event or clinical deterioration (which may include new-onset psychosis, severe suicidal ideation, or a manic or hypomanic switch), or if they or their treating psychiatrist wish them to be withdrawn.

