### Outcomes

The primary outcome will be the change on the MADRS, a 10-item, validated, observer-administered scale of depression severity, which has been extensively used in trials of depression treatment [34]. Investigators will use a structured interview guide when administering the MADRS to improve inter-rater reliability [35].

Secondary outcomes will include the change on the Quick Inventory of Depressive Symptomatology (QIDS-SR-16), a 16-item, participant-administered scale of depression severity, and the World Health Organization Disability Assessment Schedule (WHODAS 2.0), a 12-item measure of functional impairment [36,37]. Cognitive impacts of treatment will be assessed using the Screen for Cognitive Impairment in Psychiatry (SCIP) [38]. The SCIP has been well validated as a tool for measuring cognitive change in patients with depression and other psychiatric illnesses; is brief and relatively simple to perform; and includes a verbal list learning task, working memory test, verbal fluency test, delayed learning task, and visuomotor tracking test. Exploratory analyses will investigate the effect of treatment on language abilities by change in performance on an auditory lexical decision task, in which participants must differentiate real from fictitious words [39,40]. An exploratory acoustic and semantic corpus analysis will also be conducted on the recorded entrance and exit interviews.

Treatment-related manic or hypomanic switches will be captured using the Young Mania Rating Scale, an 11-item observer-administered scale of mania intensity [41]. Other treatment-related side effects will be measured using a scale derived from a systematic review of tDCS-related adverse events [42]. This scale has the benefit of asking participants to comment on the relatedness of their symptoms to their treatment and may help to distinguish between the likely side effects of tDCS and symptoms participants had before the intervention. It has also been used in other randomized control trials evaluating tDCS [43]. In addition, side effects that may be secondary to concurrent medication use will be captured using the Frequency, Intensity, and Burden of Side Effects Rating Scale and the Patient-Rated Inventory of Side Effects Scale [44,45]. Side effects captured through the use of the aforementioned scales will be summarized in an adverse events form, with additional documentation completed on any adverse events deemed to be serious in nature.

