**Postrandomization**											
	MADRS (not recorded)	—		—		✓		—		✓	
	QIDS-SR-16^j^	✓		—		✓		✓		✓	
	WHODAS^k^ 2.0	✓		—		✓		✓		✓	
	SCIP^l^	✓		—		✓		✓		✓	
	YMRS^m^	✓		—		✓		✓		✓	
	tDCS-AEQ^n^	✓		—		✓		✓		✓	
	FIBSER^o^	✓		—		✓		✓		✓	
	PRISE^p^	✓		—		✓		✓		✓	
	Auditory lexical decision task	✓		✓		✓		✓		✓	

^a^T0: baseline session.

^b^T1-30: treatment sessions 1 to 30.

^c^T60: follow-up one session, one month after trial completion.

^d^Assessment conducted.

^e^Assessment not conducted.

^f^EHI: Edinburgh Handedness Inventory.

^g^MINI: Mini International Neuropsychiatric Interview.

^h^MGH-ATRQ: Massachusetts General Hospital Antidepressant Treatment History Questionnaire.

^i^MADRS: Montgomery-Åsberg Depression Rating Scale.

^j^QIDS-SR-16: Quick Inventory of Depressive Symptomatology.

^k^WHODAS: World Health Organization Disability Assessment Schedule.

^l^SCIP: Screen for Cognitive Impairment in Psychiatry.

^m^YMRS: Young Mania Rating Scale.

^n^tDCS-AEQ: Transcranial Direct Current Stimulation Adverse Events Questionnaire.

^o^FIBSER: Frequency, Intensity, and Burden of Side Effects Rating Scale.

^p^PRISE: Patient-Rated Inventory of Side Effects Scale.

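### The observer-rated MADRS follows sessions 10, 20 and 30, so any difference between arms in visible skin redness could cue the rater: a credible risk, not a demonstrated one

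*Protocol article*

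**What the plan says.** All references are to the protocol article.

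- **Who rates.** Outcomes: "The primary outcome will be the change on the MADRS, a 10-item, validated, observer-administered scale of depression severity". A structured interview guide is used. Data Collection assigns all assessments to one pool of psychiatrists, residents and medical students.
- **When.** Data Collection: "Measurements for most scales will be conducted at the beginning of the trial (T0), after every 10 sessions (T10, T20, and T30", with a further rating one month after completion (T60). Table 1 puts the MADRS at T10, T20 and T60 in the row "MADRS (not recorded", and at T0 and T30 in the audio-recorded row.
- **What the labels mean.** Table 1, footnote b: "T1-30: treatment sessions 1 to 30". Data Collection uses the same labels for the lexical task, done "after each stimulation session (T1-30".
- **Skin effects.** Safety: "Common side effects of treatment that occur in up to 50% of patients include mild-to-moderate skin erythema, itchiness, tingling at electrode sites"; mild headache closes the list. The section adds that side effects, when they occur, are mostly brief and mild.
- **Stimulation.** Intervention and Control: "the anode will be positioned over the left DLPFC (position F3 on the 10-20 EEG system", with the cathode at F4. Active is 2 mA for 30 minutes. Sham rises to 2 mA and returns to 0.3 mA in two 17-second ramps, then stays at 0.3 mA. The Abstract and this section describe the sham as reproducing skin sensation and tingling; neither mentions redness.
- **Blinding.** Trial Design states that participants and investigators are blinded. Limitations considers whether the person stimulated can tell sham from active. It does not consider what a rater might see.

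**The concern.** Tingling and itch are felt only by the participant, but redness can be seen by someone else. The stated timing puts the three on-treatment MADRS ratings after stimulation, which is when any redness would be most evident. The sham is built to match sensation, and it delivers much less current than active. If active leaves more redness, a face-to-face rater receives information about the arm. That information remains even if the side-effect forms and the device letter are withheld.

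The primary outcome depends on the rater's judgement. A rater who suspects active treatment and scores a little lower would move the MADRS difference in favour of active. T30, the end-of-treatment rating, is among the exposed time points.

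**Working it through.** **1. The plan's own figure.** The article gives 60 completers for f = 0.25, 80% power, alpha 0.05 and r = 0.3. For the between-group effect in a repeated-measures ANOVA, the noncentrality is f²·N·m / (1 + (m − 1)·r). This needs N = 58 with m = 5 time points (power 81.9% at N = 60) and N = 62 with m = 4 (78.9%). The figure of 60 is therefore reproduced to within 2 patients. Nothing below changes it: the issue is bias, not power.

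**2. Is a difference in redness plausible?** Charge per session, from Intervention and Control:

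- Active: 2 mA × 1,800 s + ½ × 2 mA × 17 s = 3,600 + 17 = 3,617 mC (ramp taken from 0, ramp-down ignored).
- Sham: 2 × 17 s × (0.3 + 2)/2 mA + 0.3 mA × (1,800 − 34) s = 39.1 + 529.8 = about 569 mC.
- Ratio: 569 / 3,617 = about 16%.

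A difference is plausible, but sham redness need not be zero. Sham reaches the same 2 mA peak and holds 0.3 mA under the same saline-soaked pads.

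**3. How much could the cue reveal?** Let pA and pS be the proportions visibly red at the rating. The article gives neither. Assumed: pA = 30-50% (50% is the ceiling for the whole list of effects) and pS = 5-30%. With 1:1 allocation and a rater who calls red participants active:

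- P(correct guess) = 0.5 + (pA − pS)/2
- Bias in the arm difference = b × (pA − pS), where b is the rating shift for a participant believed to be on active, assumed to be 2-4 MADRS points.

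| pA | pS | Correct guess | Bias, b = 2 | Bias, b = 4 |
|---|---|---|---|---|
| 30% | 30% | 50% | 0 | 0 |
| 30% | 20% | 55% | 0.2 | 0.4 |
| 30% | 5% | 62.5% | 0.5 | 1.0 |
| 50% | 30% | 60% | 0.4 | 0.8 |
| 50% | 20% | 65% | 0.6 | 1.2 |
| 50% | 5% | 72.5% | 0.9 | 1.8 |

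The range is 50-72.5% correct guesses and 0-1.8 points of bias.

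**4. Scale.** With two equal groups, f = 0.25 corresponds to 0.5 SD. With an assumed SD of 8 that is 4 points, so the bias is 0-45% of the effect the trial is sized for (1.8 / 4 = 0.45).

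A shift of 4 points is then 0.5 SD. For a single-time comparison of 30 per arm with no true effect, the chance of a significant result is:

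- about 12% at 50% v 10% (0.20 SD)
- about 9% at 50% v 20% (0.15 SD)
- about 7% at 50% v 30% (0.10 SD)
- the nominal 5% at equal rates.

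**5. Which ratings are exposed.** T10, T20 and T30: three of the five scheduled. T0 precedes stimulation, and T60 comes a month after it ends.

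**The case against.** The strongest reply is that the article documents neither visible redness at the rating nor a difference between arms.

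- The 50% is a ceiling for several effects together, and the same section calls side effects mostly brief and mild.
- No sham rate is given.
- F3 and F4 are scalp positions, and nothing says an interviewer could see redness there.
- The timing counts completed sessions. It does not give the minutes since the electrodes came off or the order of assessments.
- Rooms, order and covering are details that an article may leave to a full protocol, which is not shown.
- Other protections exist: coded stimulators set by an uninvolved investigator, recusal of an unblinded investigator, the interview guide, the self-rated QIDS-SR-16 and an unexposed T60 MADRS.

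Most of this stands, and it limits the claim to a conditional one. A reader might infer that half of the active arm would be visibly red and that the rater is in effect unblinded, or that some minimum bias is certain. The documents support neither. The assumed ranges include equal rates, where the cue and the bias are both zero. Nor does the concession in Limitations about sham help that inference: it concerns healthy volunteers sensing their own stimulation, not raters looking at skin.

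Two things survive. The rating time is a choice the article states, not a detail it omits. And brief redness argues for separating the rating from the stimulation, because a rating soon afterwards is the one most exposed.

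**Conclusion.** The point holds as a credible risk to rater blinding on the primary outcome. The documents establish an observer-rated MADRS after sessions 10, 20 and 30, redness among the common effects, and a sham described only as imitating sensation. They do not establish how often redness occurs in either arm, how long it lasts, whether it can be seen at F3 and F4, or how soon the rating follows.

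If redness is more frequent or stronger under active and still visible at the rating, the bias would be expected to favour active. Its size is 0-1.8 MADRS points, with 50-72.5% correct guesses. That range rests wholly on the assumed redness rates (30-50% and 5-30%) and the assumed 2-4 point shift; the comparison with the planned effect also needs the assumed SD of 8. A small change to the procedure is worth making because it removes a plausible cue at little cost, not because bias has been shown.

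**What to change.** In both arms, have the person running the session cover the electrode sites with a headband or cap before the MADRS rater enters at T10, T20 and T30. State this in Data Collection and in a note to Table 1. It keeps the ratings after 10, 20 and 30 sessions and needs no extra visit. It does require that the rater is not the person who removes the electrodes that day, which the article does not say.

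The alternative is to rate before that day's electrodes are applied, again in both arms. This only reorders an existing visit. The small downside is that scores then reflect 9, 19 and 29 completed sessions, so the wording on timing would have to change, and T30 would no longer follow the full course. Covering is preferable for that reason.

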**Prerandomization**											
	Informed consent	✓^d^		—^e^		—		—		—	
	Screening of inclusion and exclusion criteria	✓		—		—		—		—	
	History and physical exam	✓		—		—		—		—	
	EHI^f^	✓		—		—		—		—	
	MINI^g^ (audio recorded)	✓		—		—		—		—	
	MGH-ATRQ^h^	✓		—		—		—		—	
	MADRS^i^ (audio recorded)	✓		—		—		✓		—	
**Postrandomization**											
	MADRS (not recorded)	—		—		✓		—		✓	
	QIDS-SR-16^j^	✓		—		✓		✓		✓	
	WHODAS^k^ 2.0	✓		—		✓		✓		✓	
	SCIP^l^	✓		—		✓		✓		✓	
	YMRS^m^	✓		—		✓		✓		✓	
	tDCS-AEQ^n^	✓		—		✓		✓		✓	
	FIBSER^o^	✓		—		✓		✓		✓	
	PRISE^p^	✓		—		✓		✓		✓	
	Auditory lexical decision task	✓		✓		✓		✓		✓	

^a^T0: baseline session.

^b^T1-30: treatment sessions 1 to 30.

^c^T60: follow-up one session, one month after trial completion.

^d^Assessment conducted.

^e^Assessment not conducted.

^f^EHI: Edinburgh Handedness Inventory.

^g^MINI: Mini International Neuropsychiatric Interview.

^h^MGH-ATRQ: Massachusetts General Hospital Antidepressant Treatment History Questionnaire.

^i^MADRS: Montgomery-Åsberg Depression Rating Scale.

^j^QIDS-SR-16: Quick Inventory of Depressive Symptomatology.

^k^WHODAS: World Health Organization Disability Assessment Schedule.

^l^SCIP: Screen for Cognitive Impairment in Psychiatry.

^m^YMRS: Young Mania Rating Scale.

^n^tDCS-AEQ: Transcranial Direct Current Stimulation Adverse Events Questionnaire.

^o^FIBSER: Frequency, Intensity, and Burden of Side Effects Rating Scale.

^p^PRISE: Patient-Rated Inventory of Side Effects Scale.

### Data Analysis and Sample Size Calculations

The primary and secondary efficacy outcomes will be analyzed using a mixed effects repeated measures ANOVA (analysis of variance), with the study group and time as fixed factors and participants as random factors, based on the intention to treat principle. Due to the wide variety of potential adverse events that can be captured, we will present this information as frequency data.

To detect a moderate effect size for the primary outcome, represented by a Cohen *f* of 0.25, with a power of 80% and significance ⍺=.05, we estimate that 60 participants will need to complete the protocol. This assumes a moderate correlation (*r*=0.3) between time points, using the power curves described in the textbook by Kirk [46]. As a study of this scope, in the ultraresistant MDD population, has not been performed before, we are unable to estimate the dropout rate. We plan to conduct an interim analysis after 30 participants complete the protocol. We will analyze the main effects of the treatment by presenting the significance of the time, treatment group, and interaction terms in the ANOVA. If there is a significant interaction, we will conduct posthoc comparisons between mean treatment and placebo outcome scores, at each time point, to characterize this effect further and will use the Tukey method to control the familywise error rate.

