### Eligibility Criteria

All participants will be required to sign an informed consent form before the final determination of their eligibility to enroll in the study. Participants will be eligible for inclusion if they:

Are adults with a major depressive episode with a score greater than 34 (signifying severe depression) on the Montgomery-Åsberg Depression Rating Scale (MADRS)Have ultratreatment-resistant MDD (defined as failure to remit despite adequate trials with 5 antidepressants at clinically effective doses, failure to remit with ECT, or failure to remit with ketamine).

Participants will not be eligible for inclusion if they:

Are currently diagnosed with psychosis, an addiction disorder (other than nicotine), borderline personality disorder, or antisocial personality disorder, as these conditions could interfere with adherence to the study protocolAre currently using a herbal compound or an agent known to modulate NMDA (N-methyl-D-aspartate) receptors, as these substances could interfere with the induction of LTP and thereby limit the effectiveness of tDCSAre pregnant, as tDCS has not been adequately studied in this populationHave an electronic implant, cardiac dysrhythmia, seizure disorder, neurological disorder, or neurosurgical history, as the safety of electrical stimulation with tDCS cannot be assured given these comorbidities.

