### Participant Recruitment and Randomization

Participants will be recruited from the inpatient population at the Grey Nuns and University of Alberta Hospitals in Edmonton, Alberta. In addition, outpatients in the city and surrounding areas will also be eligible for inclusion. Edmonton is a large and diverse Canadian city, with a metropolitan population of more than 1.3 million people. Participants may contact the study personnel directly or may be referred by their treating clinician; in the latter case, they must first give consent to disclose contact information to the study coordinators, who will then contact the participant and discuss the trial further. In cases where the treating clinician is also a study coordinator, the informed consent process will occur with a separate coordinator. Participants will be informed that they may withdraw their consent, without penalty, at any time and that this will not affect the care they receive from their treating clinician. Consent cannot be withdrawn after the conclusion of the protocol due to the blinding of participant-identifiable data.

Before randomization, participants will undergo a routine history and physical examination and complete the Edinburgh Handedness Inventory [26]. They will also be interviewed by a member of the research team using the Mini International Neuropsychiatric Interview [27]. This validated, structured tool facilitates the diagnosis of the 17 most common psychiatric pathologies and will provide confirmation that participant diagnoses fall within the acceptable purview of the inclusion and exclusion criteria. Participants will also complete a version of the Massachusetts General Hospital Antidepressant Treatment History Questionnaire, modified with the trade names of Canadian drugs [28]. To ensure that the information obtained is as accurate as possible, research personnel may also augment answers on this scale using historical medication information from a participant’s electronic health record. Finally, participants will have their baseline MADRS score recorded to ensure that it is higher than the threshold required for trial participation.

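### The random-participant ANOVA pools one variance over all visits, while the MADRS entry cut shrinks the spread at T0; if T0 is a level of time, late between-arm standard errors come out modestly too small

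*Protocol article*

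**What the plan says.** All places are in the Methods of the protocol article.

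- Data Analysis and Sample Size Calculations: the efficacy outcomes go into a mixed effects repeated measures ANOVA "with the study group and time as fixed factors and participants as random factors". If the interaction is significant, the plan is to make "posthoc comparisons between mean treatment and placebo outcome scores, at each time point", with Tukey control of the familywise error. The sample size uses a single correlation, r=0.3, between time points.
- Eligibility Criteria: adults enter with a major depressive episode and a MADRS "with a score greater than 34 (signifying severe depression").
- Participant Recruitment and Randomization: the cut is applied to the baseline value itself, since "participants will have their baseline MADRS score recorded to ensure that it is higher than the threshold required for trial participation".
- Data Collection: the measurement times are T0, T10, T20, T30 and T60.
- Outcomes: "The primary outcome will be the change on the MADRS". The section does not say whether T0 is subtracted or kept as a level of time.

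No MADRS SD is given for any visit.

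**The concern.** A model whose only random term is a participant intercept has compound symmetry: the same variance at each visit and the same correlation for each pair of visits. This trial selects on the T0 score, so the T0 variance is reduced below its untruncated value, and nothing restricts the scores afterwards. A variance pooled over all visits is then too large for T0 and too small for visits with a wider spread.

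At stake are the between-arm estimates at the end of treatment (T30) and at one-month follow-up (T60). Their standard errors and intervals would look more precise than they are.

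**Working it through.** **1. The plan's own figure.** Inputs: f=0.25, r=0.3, α=.05, power 80%, N=60. For the group effect in a repeated measures ANOVA with m visits, λ = f²·N·m / [1+(m−1)r], with 1 and N−2 df.

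- m=5: λ = 0.0625×60×5/2.2 = 8.52, power 81.9% (80% needs N=58).
- m=4: λ = 0.0625×60×4/1.9 = 7.89, power 78.9% (80% needs N=62).

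Both lie within 2 participants of the stated 60. On this reading the sample size also rests on equal variances and one correlation. It does not show whether T0 counts as a level, since the two readings bracket 60.

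**2. How far the cut shrinks T0.** For a normal with mean μ and SD σ cut below at c, the variance that remains is σ²(1 + aλ − λ²), where a=(c−μ)/σ and λ=φ(a)/[1−Φ(a)]. Assumed example μ=34, σ=8, c=34: a=0, λ=0.798, and the remaining share is 1−0.637=0.363, so the SD is 4.82. Taking the cut at 34.5 for whole-number scores, with an assumed scale maximum of 60, gives 4.68, the value used below. Over assumed μ of 28–40 and σ of 6–10, the cut leaves 19–60% of the T0 variance.

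**3. What the model uses at each visit.** In expectation, with v̄ the mean visit variance and c̄ the mean covariance, MS_subject = v̄+(m−1)c̄ and MS_residual = v̄−c̄. The model's per-visit variance is [MS_subject+(m−1)MS_residual]/m = v̄. Hence

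model SE / true SE at visit t = √(v̄ / v_t), and the actual α is about P(|Z| > 1.96 × that ratio).

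**4. Numbers.** There are 30 per arm, so SE = SD×√(2/30) = SD×0.258. All SDs are assumptions. The SDs listed are those left after selection at r=0.3, so later ones are slightly below their latent values.

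| Case | SDs T0, T10, T20, T30, T60 | v̄ | Model SE | True SE at T30/T60 | Too small by | Actual α at T30/T60 |
|---|---|---|---|---|---|---|
| A: cut only, latent mean 38, SD 6 | 4.27, then 5.87 | 31.2 | 1.44 | 1.52 | 5% | 6.3% |
| B: cut only, latent mean 34, SD 8 | 4.68, then 7.76 | 52.6 | 1.87 | 2.00 | 7% | 6.7% |
| C: later latent SDs 8, 9, 10, 10 | 4.68, 7.76, 8.73, 9.70, 9.69 | 69.3 | 2.15 | 2.50 | 14% | 9.1–9.2% |
| D: later latent SDs 8, 10, 12, 12 | 4.68, 7.76, 9.70, 11.64, 11.64 | 89.4 | 2.44 | 3.01 | 19% | 11.0–11.1% |

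Example, case C: v̄ = (21.9+60.2+76.2+94.1+93.9)/5 = 69.3. √69.3 = 8.32, and 8.32/9.70 = 0.86.

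The α values for A, C and D come from simulation (40,000 null trials, complete data); B is from the formula. Over all cut-only cases simulated, late α was 6.2–7.1% and the SE shortfall 5–8%. The limit of squeezing T0 alone (T0 variance zero) is √(4/5)=0.894, an α of about 8%. The T0 comparison is far too conservative (0.1–1.2% in the cut-only cases). In C and D the T10 standard error is too large (ratios 1.07 and 1.22), so the understatement concerns the late visits.

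**5. The omnibus tests.** Group main effect: 4.8–5.2%. Interaction at r=0.3: 4.9–5.7%. Interaction with strong correlation that decays with lag (from about 0.6 to 0.8) and growing SDs: about 6.5–8%.

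**6. The sequence as planned.** In the simulated cases with T0 as a level, an interaction gate followed by any late p<.05 occurred in about 4–5.5% of null trials. Adding Tukey over all ten cell means brought this to about 0.6–1.5%.

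**7. Change scores instead.** With T0 subtracted and four later visits, equal later SDs give 5.0–5.2% per visit. Later latent SDs of 8, 9, 10, 10 give about 6.6% at T30 and T60.

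**The case against.** The strongest reply is that a journal article is being read as a full specification. It does not name compound symmetry, nor does it rule out a sphericity correction, and an analysis plan not shown here could supply one. That is fair, and the lack of such detail is not the point. The point is that the model the article does state carries the common-variance assumption.

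Second, T0 may not be a level of time. If change scores over the post-baseline visits are analysed, the truncation effect vanishes and only growth in later variances matters. This stands. The wording about scores at each time point leans the other way without settling it.

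A reader might go further and infer any of the following. The documents do not support them.

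- *The stated α of .05 is not delivered overall.* The main-effect test is unaffected and the interaction is near nominal at the article's own r=0.3. Inflation to 6.5–8% needs strong, lag-decaying correlations that the article does not state. In the planned sequence, gate plus Tukey over all ten cell means kept false visit findings well below 5%: 2.6% in the harshest case tried (SDs 4, 6, 8, 10, 12, lag correlation 0.8). With the gate but no Tukey, that case reached 7.2%.
- *The entry cut by itself causes errors of 9% or more at T30 and T60.* The cut alone gives 6–7%, with a ceiling near 8%. The larger figures need follow-up spread to grow as well.
- *T0 spread must be below follow-up spread.* Truncation shrinks T0 relative to its own untruncated spread. No follow-up SD is given, so the comparison across visits is likely but not certain.

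**Conclusion.** The concern holds in a limited form. The stated ANOVA pools one variance over visits, and the trial's own entry rule works against that assumption at T0. If T0 is a level of time, the late between-arm standard errors are understated: modestly from truncation alone, and more at T30 and T60 if the spread also widens during follow-up. The direction for any visit whose variance exceeds the average is algebra. The size depends on the assumed SDs, complete data and 30 per arm.

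The gate and the Tukey step restrain the overall false-positive rate, but neither changes a standard error. Estimates and intervals at T30 and T60 would still look too precise. This should be corrected because the remedy is cheap; it does not by itself undermine the trial's omnibus tests.

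**What to change.** Analyse the MADRS with a mixed model for repeated measures with unstructured within-participant covariance and Kenward-Roger degrees of freedom. Name the fallback if it does not converge, for example heterogeneous Toeplitz, then heterogeneous autoregressive. Take the T30 and T60 contrasts from that model with visit-specific variances. State whether T0 is a level of time or is subtracted.

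If the classical ANOVA is kept, apply the Greenhouse-Geisser correction and use visit-specific error terms for the comparisons at each visit.

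In simulation, visit-specific variances returned late per-visit error to 4.8–5.1%. In the strongly correlated scenarios, the interaction test was at 4.9–5.1% with unstructured covariance (Hotelling T²) and 4.7–4.8% with Greenhouse-Geisser.

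The cost is analysis wording. With five visits an unstructured matrix has 5×6/2 = 15 parameters, so with 60 participants there is a small loss of degrees of freedom and a need for the convergence fallback. No extra data or participants are needed, and the change can be made before unblinding.
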